## Abstract

Dry needling (DN) is an emerging technique commonly used in neurological and musculoskeletal pain conditions, but there have been no previous studies in patients with multiple sclerosis (pwMS). This trial aims to assess the efficacy of deep DN, compared with sham placebo DN, on gait performance, spasticity level, pain, electromyographic activity, range-of-movement (ROM) and quality of life in pwMS. Forty adults with MS were randomly assigned to one study group. The DN group will undergo 2 sessions (once per week) using DN over the rectus femoris (RF) and gastrocnemius medialis (GM) muscles at the lower extremity with higher spasticity. The placebo group will receive the same protocol using a sham placebo needle (Dong Bang needle). Outcome measures will include gait performance, using the GaitRite^®^ system, spasticity level with the Modified Ashworth Scale, superficial electromyographic activity of RF and GM, pain (pressure algometer), ROM (goniometer), and quality of life (Musiqol). This study is the first investigating the short-term effect of DN, compared with placebo, in pwMS, and taking into account the possible changes in the electromyographic activity of the lower limb. Therefore, the results may help to understand the suitability of using this technique in the clinical setting for this population. Trial registration: ACTRN12619000880145.

## 1. Introduction

Multiple sclerosis (MS) is one of the most common and disabling neurologic conditions among early adults, affecting approximately 2.3 million people worldwide [1], and with a higher prevalence in women (3:1 ratio) [2]. The specific cause of the disease is still uncertain, and thus the individual course and prognosis are difficult to predict [3]. Persons with MS (pwMS) suffer from varying cognitive and sensory-motor impairments that affect their functional capacity, including impaired gait performance [4]. This is reported as a major complaint in up to 85% of pwMS [5], and seems to be closely related to increased fall risk [6]. Chronic pain, especially at the lower extremities (LE), is also a very disabling symptom within this population, with an overall prevalence of 50% [7]. Spasticity and muscle weakness are present from the initial stages of the disease and have been associated with abnormal gait patterns [8], which may worsen other symptoms and impact on the quality of life (QOL). For example, the presence of spasticity contributes to modifying the speed, cadence, stride length, and swing phase during gait, and to a lower hip and knee range-of-movement (ROM) [9]. Additionally, walking-related motor fatigue in pwMS is attributed to the higher proportion of force that LE muscles, especially the soleus and gastrocnemius muscles, have to generate during prolonged walking [10].

The clinical management of MS-related disorders includes pharmacological and non-pharmacological interventions. In severely disabled patients, rehabilitation aims to rebalance the altered metabolic and muscle parameters [11], and the main goal is to improve functional independence and QOL [12]. Overall, physiotherapy treatments can be categorized into four domains: physical training (fitness, endurance, or resistance training), neuroproprioceptive facilitation or inhibition, motor skill acquisition, also called guided individualized therapy, and technology-based interventions [13]. However, the evidence for most approaches is still limited for the management of aspects such as walking capability [12], spasticity level [14], and self-reported pain intensity [15,16]. In addition, the recommendations about the necessity of improving the access to treatment for pwMS, to adapt the interventions to the individual disability level, and to use up-to-date evidence-based approaches do not seem to be properly implemented in the clinical setting [17,18].

Dry needling (DN) is a novel but commonly used technique for patients with musculoskeletal pain, although there is conflicting evidence about its effectiveness [19,20]. In people with central nervous system disorders, the efficacy of DN has been scarcely investigated in stroke survivors, with purported positive effects on spasticity, pain, and ROM [21,22,23]. Even though DN is mostly a safe technique, minor adverse events, e.g., bruising, bleeding, and pain, are common [24], and need to be considered.

The specific effect of DN, when compared with sham placebo DN, has been barely assessed in people with neurological conditions [25]. Patients’ expectations regarding the treatment may influence the results and evoke changes associated with the placebo effect. In fact, it has been suggested that the patient–practitioner relationship may be enough to improve the QOL and the results after intervention in some patients [26], although there is certain discrepancy about this topic [27]. In chronic musculoskeletal disorders, there are no definite conclusions on the superiority of using real deep DN over placebo DN [28]. Therefore, more studies that compare these two approaches are needed to better understand this issue.

To our knowledge, no previous randomized controlled trials have investigated the effects of using deep DN in pwMS. Recently, our research group reported promising findings in a clinical case study following the same protocol [29]. DN aims to induce a localized stretch of the soft tissue and may help to modulate the motoneuron activity and decrease the excitability of spinal reflexes, even though the exact physiological mechanisms that support this technique remain unknown [30]. The use of DN also seems to optimize the results of rehabilitation protocols. For example, in people with fibromyalgia, DN has been proposed as a suitable complementary approach to improve pain and QOL [31,32]. However, it is still necessary to continue evaluating the potential clinical effects of DN in many other conditions [30]. We hypothesize that using deep DN over the rectus femoris (RF) and Gastrocnemius Medialis (GM) muscles, which are directly related to the functionality of the LE, may help to evoke motor control changes that improve gait performance in pwMS. Therefore, our aim is to analyze the short-term effects of deep DN, compared to sham placebo DN, on gait parameters, spasticity level, electromyographic activity, pain intensity, ROM, and QOL in adults with MS.

## 2. Materials and Methods

### 2.1. Study Design

This is a protocol for a placebo-controlled, double-blind, superiority, randomized clinical trial. The study protocols follows the guidelines of the SPIRIT Statement [33]. This study protocol was approved by the Andalusian Biomedical Research Ethics Committee 04/2019 (CEI Hospitales Universitarios Virgen Macarena—Virgen del Rocío, Seville, Spain) and was registered on the Australian New Zealand Clinical Trials Registry (ACTRN12619000880145).

### 2.2. Setting and Eligibility Criteria

The data will be collected in the Multiple Sclerosis Research and Treatment Unit, Dinac Foundation, Vithas Nisa Hospital, Castilleja de la Cuesta, Seville, Spain. Eligibility criteria are as follows: patients with a diagnosis of MS according to the McDonald 2010 criteria [34]; males and females older than 18 years; ability to walk for at least 2 min (with or without support), which represents an Expanded Disability Status Scale (EDSS) [35] score between 0–6.5; absence of MS outbreaks in the previous month; having signed the informed consent form; and being able to comply with the study protocol. Exclusion criteria are: pregnancy; patients with comorbidity signs in the last month; having received corticosteroid treatment within the previous month; inability to walk due to physical impairments; and having received botulinum toxin injections at the LE in the last 3 months.

### 2.3. Procedure

The flowchart of the study process is shown in Figure 1 and Figure 2. At a first appointment, a neurologist will carry out a complete neurological evaluation of each patient to assess for eligibility. Data collection will be carried out at baseline (first visit) and between 6 and 8 days after the intervention protocol by a researcher (evaluator) who will be blinded to participants’ allocation group. The intervention in both groups will be performed by another senior physiotherapist, who is experienced in the use of DN.

The lead researcher (physical therapist) will get the signed informed consent forms, where the study details will be clearly explained, and the patients will be informed that his/her participation is voluntary so they can withdraw at any moment with no need to provide any specific reason.

### 2.4. Interventions

All patients will continue receiving their usual care during the study protocol. In addition, the DN interventions in both groups will be carried out in the Research and Treatment Unit in Multiple Sclerosis, Dinac Foundation, at Vithas Nisa Hospital, Seville, Spain.

For those in the DN group, the intervention will consist of using deep DN with disposable stainless-steel needles (0.3 mm × 50 mm or 0.3 mm × 40 mm, Agupunt, Barcelona, Spain), depending on the depth of the muscle to be treated. The fast in–fast out Hong technique will be used over the active or latent myofascial trigger points of the RF and GM muscles, following the diagnostic criteria and intervention guidelines previously established [36]. A minimum of 3 to 4 local twitch responses will have to be elicited. The participants’ level of tolerance will be considered, and participants will be able to request to stop the treatment at any moment if unpleasant or very painful sensations appear. The intervention will be performed in the LE with higher spasticity, as expressed by the Modified Ashworth Scale score in the targeted muscles. A single puncture per muscle will be made each session. DN will be performed during 45–60 s for muscle until the local twitch responses disappeared or until the patient can no longer bear the pain. The intervention will last for 2 weeks, 1 session per week.

For the placebo group, a simulation needle procedure using a Dong Bang placebo needle, similar to the Streitberger needle, will be used. These needles appear to be effective placebo techniques in studies using acupuncture [37]. The physical therapist will follow the same treatment protocol than in the DN group. The placebo needles evoke mechanical stimulation without piercing the skin; hence, patients experience a pressure sensation similar to that of a “real” needle.

### 2.5. Outcomes

Clinical assessment of gait performance, spasticity level, electromyographic activity, pain, ROM, and QOL will be reported in the first and third visit (Figure 2). Several outcome measures will be collected to get a better understanding of the treatment effect and because of their extensive use in research on these topics. This will allow us to compare our results with those reported in previous studies. Following the guidelines of the International Classification of Functioning, Disability and Health [38], some of the outcomes will be devoted to investigate functional parameters, such as gait parameters and QOL. The outcome measures and the tools to assess them are detailed below:

#### 2.5.1. Gait Performance

The GaitRite^®^ system will be used to measure several gait parameters (average gait speed, walking cadence, step length, stride length, step width, and percentage of support-oscillation) [39,40]. During the overground walking assessment, participants will walk at preferred speed along an 8.62 m walkway (the length of the tapestry). Data about gait parameters will be collected with motion sensors placed directly in the tapestry.

The two-minutes walking test (2MWT) [41] will be used to assess functional capacity. Given the difficulty that many patients with MS have to walk for 6 min, we propose the 2MWT in the present protocol. The 2MWT is valid in pwMS and provide an efficient and alternative to the 6MWT.

#### 2.5.2. Spasticity

The Modified Ashworth scale (MAS) [42] will be used to assess the spasticity level over the RF and GM muscles. The reliability of the MAS has been demonstrated in LE muscles, e.g., knee extensors and plantar flexors. Thus, this scale is a valid tool for the present protocol. Even though the MAS only measures the passive component of spasticity, the electromyographic evaluation detailed below would provide some information on the spastic co-contraction phenomena during the execution of analytical movements.

#### 2.5.3. Electromyographic Activity

A superficial Electromyography (sEMG) will measure the neuromuscular activity over the RF and GM muscles and their activity during gait. This outcome will be collected with a sEMG device called mDurance [43,44]. The sEMG sensors will be placed in the motor point of the RF and GM muscles according to the recommendations of the SENIAM protocol [45]. To obtain the Maximal Voluntary Contraction [46] for the RF muscle, patients will lie on their back with the leg off the table (hip in extension, and knee in 90° flexion), in the stretch position, and the patient will be asked for a maximum muscle contraction and to keep it for 6 s. For the GM muscle, the patient will be placed lying on his back. With the ankle in dorsal flexion, the patient will be asked to move the ankle to plantar flexion, and to keep the muscle contraction for 6 s. Additionally, the activity of the RF and GM muscles will be monitored during gait, both during the first minute of the 2 MWT and during the GaitRite^®^ examination. In both situations, the Root Mean Square [10] for those muscles will be measured to indirectly quantify muscle fatigue.

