## 3. Discussion

This innovative study will evaluate the impact of DN on gait performance, spasticity level, electromyographic activity, pain, ROM, and QoL in pwMS. Including a sham placebo DN group will allow us to discuss which effects may be related to patient’s expectations and the possible motor behavior adaptations due to this effect. We selected the RF and GM as the targeted muscles for their role in the functionality of the LE in this population. These two muscles are largely responsible for the so-called stiff knee pattern [49,50] caused by an excessive activation of knee extensors during the pre-swing phase [50], along with weakness of the gastrocnemius muscles [49]. This pattern is especially prevalent in pwMS. As regards the treatment protocol, there is some controversy about the number of sessions required to evoke changes after DN interventions, which range from 1 to 3 sessions in most of previous research in this field [23]. In our protocol, we will assess the changes after 2 treatment sessions.

Gait performance and the electromyographic activity of RF and GM muscles have been included as outcomes to detect the electrophysiological changes that may occur at the muscular level, although the specific mechanisms of action of the DN intervention remains controversial [30]. This will allow us to investigate the motor pattern changes. This appears to be an important outcome after using an invasive technique that acts directly over the muscle tissue which could evoke changes in the gait pattern. Thus, the interpretation of the electromyographic parameters by means of maximum voluntary contraction and root mean square may inform us about changes related to muscle force and fatigue. Additionally, functional electromyographic measurements during gait will help us to understand how these changes can influence gait patterns.

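### Gait sEMG amplitude is to be read as muscle fatigue, but from windows poorly placed to capture it and with no within-walk contrast described

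*Protocol article*

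**What the plan says.** Section 2.5.3 of the protocol article sets two recording windows for sEMG of the rectus femoris (RF) and gastrocnemius medialis (GM) in gait: "the activity of the RF and GM muscles will be monitored during gait, both during the first minute of the 2 MWT", and the GaitRite examination. It then gives their purpose: "In both situations, the Root Mean Square [10] for those muscles will be measured to indirectly quantify muscle fatigue".

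Section 2.5.1 describes the GaitRite assessment as walking at preferred speed on a walkway of 8.62 m. It does not give the number of passes. The 2MWT, in the same section, "will be used to assess functional capacity". Section 2.2 makes the ability to walk for at least two minutes an entry condition.

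The Introduction cites for walking-related motor fatigue the same reference that section 2.5.3 attaches to RMS. It attributes that fatigue to the share of force that leg muscles "have to generate during prolonged walking". The Discussion plans to interpret maximal voluntary contraction (MVC) and RMS on the ground that they "may inform us about changes related to muscle force and fatigue". Section 2.8.2 compares pre-post differences within and between groups.

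**The concern.** Fatigue is a change over a bout of effort. To see it, one needs an early and a late segment of the same bout, with enough effort in between. The article ties fatigue to prolonged walking and then records sEMG in the first half of a two-minute test and on a short walkway. It describes no comparison of a later with an earlier part of either recording, and gives no reason for stopping sEMG at one minute.

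What is at stake is interpretation. The Introduction suggests that dry needling may modulate motoneuron activity, so the general level of activation may well move with treatment. If RMS is summarised as a level and called fatigue, a change in activation would be reported as a change in fatigue, and an absent difference in level would not exclude an effect on fatigue.

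**Working it through.** The plan states no figure on this point, so there is none to reproduce. Sample size and power do not enter.

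**1. Length of the windows.**
- 2MWT: 60 s of 120 s, or 50%, all in the first half.
- GaitRite: duration of one pass = 8.62 m / speed. The article gives no speed, so I assume 0.3 to 1.3 m/s.

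| Assumed speed (m/s) | One pass (s) | Share of 120 s |
|---|---|---|
| 0.3 | 28.7 | 23.9% |
| 0.5 | 17.2 | 14.4% |
| 0.8 | 10.8 | 9.0% |
| 1.0 | 8.6 | 7.2% |
| 1.3 | 6.6 | 5.5% |

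Filling 60 s on the walkway would take 60 × speed / 8.62 passes, which is 2.1 at 0.3 m/s and 9.0 at 1.3 m/s.

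**2. What a level can show.** Assume, for illustration only, that RMS at time *t* (minutes) is *a* + *bt*, where *a* is the fresh activation level and *b* the drift attributed to fatigue.
- Mean over the first minute: *a* + 0.5*b*. Its pre-post change is Δ*a* + 0.5Δ*b*.
- Δ*a* = δ with Δ*b* = 0 gives a change of δ. Δ*a* = 0 with Δ*b* = 2δ also gives δ. One average cannot tell the two apart.
- Dividing by an MVC value *M* gives (*a* + 0.5*b*)/*M*. That rescales both terms and still does not separate them.

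**3. What a contrast within one walk can show.**
- Mean over the first 30 s: *a* + 0.25*b*. Mean over the last 30 s of the 2MWT: *a* + 1.75*b*.
- Difference: 1.75*b* − 0.25*b* = 1.5*b*. The level *a* drops out.
- Ratio: (*a* + 1.75*b*)/(*a* + 0.25*b*). A multiplicative gain, such as one from sensor placement at that visit, cancels here but not in the difference. The ratio still depends on *b* relative to *a*, so the 1.5*b* does not describe it.
- Splitting only the recorded first minute into halves: (*a* + 0.75*b*) − (*a* + 0.25*b*) = 0.5*b*.

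These expressions show what each summary can identify. They are not a comparison of precision, since they carry no noise term.

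**4. Against the text.** The article describes no early-versus-late contrast and no sEMG in the second minute of the 2MWT. The entry criterion means that enrolled patients should be able to supply that second minute.

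**The case against.** The strongest reply is that nothing in the article shows the first minute to be free of fatigue. No onset time is given. Patients up to EDSS 6.5 are eligible and need only manage two minutes of walking, with or without support, and the 2MWT was chosen because many cannot easily walk for six. Some may tire within a minute, and the illustrative model itself has drift building up from the start. This stands. It also stands that the number of GaitRite passes is unknown, and that a fatigued second minute is an assumption. What is certain is only that the second minute follows more accumulated walking than the first.

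A second reply is that the article never says RMS will be collapsed to one mean. A full protocol or analysis plan could split the recorded minute. That is fair, and it is why the point rests mainly on the windows, which section 2.5.3 does fix. An analysis plan cannot recover a second minute that was not recorded.

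Third, the wording is cautious, fatigue is not among the stated aims, and sEMG does not drive the sample size. That limits the weight of the point, but the fatigue reading is still stated twice.

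Fourth, a late-to-early contrast has its own confounder. The 2MWT is not described as fixed-pace, and a patient who slows may show lower RMS while fatigue rises. This is correct, and the fix has to allow for it.

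**Conclusion.** The point holds in a limited form. The sEMG windows are poorly placed to capture fatigue as the article itself describes it: half of the 2MWT is left out, and no within-walk contrast is described. An RMS level from these windows cannot distinguish altered activation from altered fatigue. The pass durations rest on assumed speeds, and the algebra on an assumed linear drift. That a single level mixes the two components does not depend on linearity.

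A reader might go further and infer that both windows close before fatigue can develop, or that a null RMS result would mean nothing. The documents do not support either reading. They give no onset time, and the randomised comparison of RMS as muscle activity, which is the outcome named in the aims, remains valid. Nor is the 2MWT itself cut short, since only the sEMG recording stops at one minute. The change is worth making because it is specific and cheap, but it does not touch the outcomes on which section 2.8.1 sizes the trial.

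**What to change.** - In section 2.5.3, record sEMG over the full 2MWT. Define the fatigue index for RF and GM as late versus early RMS within the same walk, for example the last 30 s divided by the first 30 s.
- Compare the pre-post change in that index between arms, and interpret it alongside any change in walking speed during the test.
- Report RMS from the GaitRite walk, and from any patient with only a first-minute recording, as muscle activity and not as fatigue. Bring the Discussion into line.

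Cost: 60 more seconds of recording in a test already done with sensors on, one derived variable, some account of speed within the test, and a few sentences of text. The ratio may be noisier than a mean and is sensitive to slowing. The Abstract speaks of randomisation in the past tense, so some assessments may already be complete. Where the second minute was not recorded, the index cannot be derived and only the relabelling applies.

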#### 2.5.4. Pain

The pressure pain threshold, as the minimal amount of pressure where the sensation of pressure changes to pain, will be collected with a pressure algometer (Psymtec Digital Algometer M3) [47]. The measurement will be performed bilaterally at several spots: (a) over the motor point of the RF muscle and GM muscles; (b) at the head of the splint bone, considered as a control point close to the intervention sites; and (c) distally, over the upper trapezius, as a remote control location.

#### 2.5.5. Range of Movement

The passive hip, knee, and ankle ROM will be assessed using a manual standard goniometer. ROM is a common outcome measure in other studies about the efficacy of DN in different conditions.

#### 2.5.6. Quality of Life

The Multiple Sclerosis International QoL (Musiqol) [48] questionnaire will measure changes in the QOL. This is a multi-dimensional and self-administered questionnaire, and is available in 14 languages, including Spanish. This tool is a disease-specific QOL scale that includes items related to activities of daily living and psychological aspects, among others.

